## Data collection method

### Severe maternal morbidity and preventive actions and case management for PPH

We use the near-miss form as proposed by WHO to collect outcome data [34]. We include some background information, including use of induction/augmentation of labour, estimated blood loss and patient’s age and parity. We also added variables to capture the number of units of blood transfused and the haemoglobin at discharge for mothers who experienced haemorrhage or received a blood transfusion.

We trained two members of the maternity staff, midwives or clinicians, to be data collectors in each of the included health facilities. Their role is to abstract the relevant information each morning from the patient notes according to a standard protocol. Data collectors visit antenatal, labour and postnatal wards, the female general and female wards and the laboratory as well as attending the morning report session to ensure that all cases of near misses and female deaths are reviewed. All cases which could potentially qualify as a near miss are to be captured by the data collectors, including every case of haemorrhage regardless of the severity. Data are abstracted from multiple sources including admission, discharge and birth registries as well as case notes. The data collectors use a paper-based form and then enter the anonymised data immediately at discharge or death into the tablet-based application (Lenovo A3500-F). The application uses ranges and completeness checks to ensure data quality and completeness. The data collectors upload the data from the tablet to the cloud on a bi-weekly basis.

Training for data collectors is initially provided during a one-and-a-half day training session which includes (1) the concept of near miss, (2) collecting data using the near-miss forms and (3) the tablet application, procedure for uploading data, data safety and handling of missing data. We put an emphasis on the definition of PPH and its recognition in order to improve recording of PPH. Data collectors are retrained in a one-day refresher session after 5 months of data collection by reviewing forms with the data collectors and discussing their experiences and problems encountered.

To ensure compliance with the data collection protocol, project staff will conduct monthly visits at the beginning, then 3-monthly supervision visits as well as monthly telephone calls to the data collectors. Registers and files are reviewed together at in-person meetings to check for missed cases or missing information. Data collectors in the health centres are linked to the nearest study hospital for support, and WhatsApp groups are established for exchange on technical issues between data collectors and research team.

Data on the denominator — the total number of deliveries in the facilities — is collected through the monthly telephone call and verified during supervision visits. Near-miss data are checked once a month against the reported number of severe events to ensure all data has been uploaded successfully. In addition, we have an external team perform a quality control for completeness by randomly selecting a sample of one third of the facilities. They then review the registers and case notes and extract the respective information to define cases for the last month to compare results with the information submitted by the facility-based data collectors.

### Knowledge, skills and confidence in preventing and managing PPH

We will evaluate the knowledge, skills and confidence of health care providers before and after the competency training on the same day of the training using the standard Jhpiego tool. The confidence assessment involves self-rating on performance of AMTSL and PPH management.

### Facility readiness for prevention and care of PPH

We will evaluate the readiness of facilities to provide care for PPH complications using a health facility assessment tool adapted from tools used earlier in Tanzania and Uganda [25, 37]. We included items which indicate the availability of PPH services, including blood transfusion, human resources, drugs and supplies, protocols for preventive and curative action for PPH and emergency preparedness (emergency trays, referral readiness including transport and communication). Each facility involved in the study is visited twice: once at the start of the baseline period of data collection and again at the end of the 9-month intervention period to collect this data.

We established a scientific advisory committee to monitor the trial. Stopping rules were not agreed on, as the intervention was a single event and no harms were expected. Endline data collection is ongoing in Tanzania (February to October 2016) and is planned to start in Uganda in December 2016 and to run up to September 2017.

### Sample size

We estimate six cases of near miss per 100 deliveries of which two will be PPH-related. This cautious assumption is based on studies from Africa where the PPH-related near misses per 100 deliveries ranged from 2% in a rural referral hospital in Tanzania [35], to 5% in Zimbabwe and Zambia [38], and 9% at a tertiary hospital level in Nigeria [39]. This range is broadly supported by a recent systematic review of severe maternal morbidity in sub-Saharan Africa [6].

We assumed that the training would reduce severe morbidity (defined as near miss) by 25%. This estimate was chosen because similar training had an effect on neonatal mortality of a similar size [11]. Secondly, it has been shown that consistent use of AMTSL should reduce severe outcomes by half [40]. Other interventions included in the training, such as prompt identification of haemorrhage and immediate treatment with oxytocin, should further reduce severe outcomes [7]; thus a reduction of 25% was deemed to be possible.

We used the formula proposed by Hayes and Moulton for matched clusters [41] to calculate the number of clusters needed in order to obtain a power of 80% in our analysis. Considering the estimated coefficient of variation of near misses between clusters, we estimate that the intervention will reduce overall near misses and PPH near misses per 100 deliveries by 25% in the intervention compared to comparison clusters (districts). Anticipating 3000 deliveries in each cluster (hospital and health centres), the following formula was used:$$ \mathrm{c}=2+{\left({\mathrm{z}}_{\alpha /2}+{\mathrm{z}}_{\beta}\right)}^2\;\mathrm{x}\;\left[{\mathrm{p}}_0\left(1-{\mathrm{p}}_0\right)/\mathrm{n}+{\mathrm{p}}_1\left(1-{\mathrm{p}}_1\right)/\mathrm{n}+{\mathrm{k}}^2\left({{\mathrm{p}}_0}^2+{{\mathrm{p}}_1}^2\right)\;\right]/{\left({\mathrm{p}}_0-{\mathrm{p}}_1\right)}^2 $$

where z_α_/2 + z_β_ = (1.96 + 0.84) assuming a power of 80% and 5% error.

Considering the prevalence of near-miss haemorrhage equal to 2% in the comparison group, and assuming a *k* (the coefficient of the variation of the proportion of near misses between clusters) value of 0.15 [42], we calculated that the required number of clusters required is equal to 10 per group.
*p*
_0_ = 0.02
*p*
_1_ = 0.015 (reduction of 25%)
*n* = 3000 deliveries in a cluster
*k* = 0.15

Considering instead the prevalence of overall near miss equal to 6% in the comparison group, the number of clusters required is equal to 8 per group.
*p*
_0_ = 0.06
*p*
_1_ = 0.045 (reduction of 25%)
*n* = 3000 deliveries in a cluster
*k* = 0.15

### Randomisation

We use unblinded matched-pair randomisation of districts (clusters), which is done separately in each country. Criteria for matching were health care organisation (number of hospitals and health centres), urban/rural district, geographical area and a balance in the outcome measurement ‘PPH-related near-miss cases among women who suffered PPH’ available from the baseline data collection. Randomisation is done using Stata by the trial statistician, who is otherwise not involved in the study implementation. Blinding of participants is not possible due to the nature of the intervention.

### Analytical methods

Statistical analysis will be performed using Stata version 13 (College Station, TX, USA). An analytical plan is prepared for review by the international scientific advisory board.

Descriptive analyses included frequencies for categorical variables, and mean and standard deviation or median and inter-quartile range for continuous variables will be performed. The main analysis will compare districts with their included hospitals and health centres allocated to the HMS BAB training with the comparison districts, which will only receive the training at the end of the study. The analysis will be conducted on an ‘intention-to-treat’ basis. We will conduct an interrupted time series analysis in order to compare the changes in the proportion of near misses before and after the intervention period between the two groups (intervention and comparison) at the cluster level. The analysis will use the difference-in-differences estimate comparing changes within each district.

In order to compare individual-level skills and competence of trained health care providers (using the pre-post training evaluation), we will use multilevel mixed-effects generalised linear models (Stata command *meglm*) with different family distributions according to the outcome distribution (Stata option *family*). Results will be presented as effect estimates with 95% confidence intervals and will be done separately for each country. Sub-group analyses for primary outcomes will be done for type of district (urban/rural). Interaction tests will be performed if relevant.

Comparing outcomes calculated at the cluster level is recommended if the cluster size is limited to 18–20 clusters. The restricted (matched) cluster-randomised allocation to implementation and comparison districts should ensure that both are comparable with respect to key factors. However, this assumption will be assessed by comparing key input characteristics such as human resources and major equipment and services available using chi-squared tests or, if significant, adding these characteristics to the regression models mentioned above to adjust for their confounding effect. The analysis of secondary endpoints of management practices will follow the same approach.

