**Methods/design:**

In Tanzania and Uganda we randomise 20 and 18 districts (clusters) respectively, with half receiving the training intervention. We use unblinded matched-pair randomisation to balance district health system characteristics and the main outcome, which is in-facility severe morbidity due to haemorrhage defined by the World Health Organizationation-promoted disease and management-based near-miss criteria. Data are collected continuously in the intervention and comparison districts throughout the 6-month baseline and the 9-month intervention phase, which commences after the training intervention. Trained facility midwives or clinicians review severe maternal complications to identify near misses on a daily basis. They abstract the case information from case notes and enter it onto programmed tablets where it is uploaded.

Intention-to-treat analysis will be used, taking the matched design into consideration using paired *t* test statistics to compare the outcomes between the intervention and comparison districts. We also assess the impact pathway from the effects of the training on the health provider’s skills, care and interventions and health system readiness.

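### The abstract names a paired t test as the main analysis and the methods name an interrupted time series with difference-in-differences; the stated 80% power belongs only to the paired follow-up comparison

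*Protocol article*

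**What the plan says.** Three places in the protocol article bear on the main comparison.

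- **Abstract, Methods/design.** "Intention-to-treat analysis will be used, taking the matched design into consideration", and the test follows: "using paired *t* test statistics to compare the outcomes between the intervention and comparison districts".
- **Analytical methods.** The main analysis is described differently: "We will conduct an interrupted time series analysis in order to compare the changes in the proportion of near misses" before and after the intervention, at cluster level, and then "The analysis will use the difference-in-differences estimate comparing changes within each district". The section mentions matching only as a reason to expect comparable arms. It also speaks of adding covariates to regression models already mentioned, but the only models named before that are for provider skills.
- **Sample size.** "We used the formula proposed by Hayes and Moulton for matched clusters", "assuming a power of 80% and 5% error". The printed formula contains p0, p1, one cluster size n and k. For PPH near miss, "we calculated that the required number of clusters required is equal to 10 per group"; for overall near miss the answer is 8.

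**The concern.** A paired t test of follow-up rates, a difference-in-differences (DiD) contrast and an interrupted time series are different estimators with different variances. The article does not say which one carries the conclusion. The point matters more here because allocation is unblinded and facility staff collect the outcome.

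The power statement can belong to only one of them. DiD subtracts a 6-month baseline rate that has its own sampling error. When events are few, the subtraction can add more noise than it removes. If DiD is the real primary analysis, the trial may have less power for its haemorrhage outcome than the article states.

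**Working it through.** **Inputs.** From Sample size: p0 = 0.02, p1 = 0.015, n = 3000, k = 0.15, z-sum = 1.96 + 0.84. From Randomisation and the abstract: 10 pairs in Tanzania and 9 in Uganda, randomised separately. Derived: Inclusion of participants gives 3000 deliveries per 9 months, so a 6-month baseline has about 3000 × 6/9 = 2000. Not stated: rho, the correlation of true district rates between baseline and follow-up, so the range 0 to 1 is shown.

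**1. The plan's own figure.** Variance of a within-pair follow-up difference:

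V_post = 0.0196/3000 + 0.014775/3000 + 0.0225 × (0.0004 + 0.000225) = 1.146e-5 + 1.406e-5 = 2.552e-5.

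c = 2 + 7.84 × 2.552e-5 / 0.005² = 10.0, as stated. For 6% against 4.5%, V_post = 1.597e-4 and c = 7.6, stated as 8. Both reproduce.

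Inverting the formula, power = Φ(√[(c − 2)(p0 − p1)²/V] − 1.96). At c = 10 this is Φ(2.80 − 1.96) = 80% (79.5% by the noncentral t). At c = 9 it is about 74%.

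**2. Difference-in-differences, PPH near miss.**

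V_base = 2 × [0.0196/2000 + 0.0225 × 0.0004] = 2 × [9.8e-6 + 9.0e-6] = 3.76e-5.

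cov = rho × 0.0225 × (0.0004 + 0.0003) = rho × 1.575e-5.

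V_DiD = V_post + V_base − 2 cov.

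| rho | V_DiD | ratio to V_post | clusters per group | power, 10 pairs | power, 9 pairs |
|---|---|---|---|---|---|
| 0 | 6.31e-5 | 2.47 | 21.8 | 43% | 38% |
| 0.5 | 4.74e-5 | 1.86 | 16.9 | 54% | 48% |
| 0.8 | 3.79e-5 | 1.49 | 13.9 | 63% | 57% |
| 1 | 3.16e-5 | 1.24 | 11.9 | 71% | 65% |

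The baseline sampling variance per district (9.8e-6) exceeds the between-district variance (9.0e-6). That is why DiD loses even at rho = 1.

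**3. Where the shortfall goes away.**

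- *Overall near miss.* Baseline sampling variance is 2.82e-5 against a between-district variance of 8.1e-5. DiD at 10 pairs has 59% power at rho = 0, 79% at 0.5, 84% at 0.6 and 93% at 0.8. It beats follow-up-only above rho of about 0.77.
- *All 19 pairs pooled, PPH near miss.* DiD has 74% at rho = 0, 80% at 0.3 and 96% at 1.
- *Larger districts.* If each had 5000 follow-up deliveries (an assumption), DiD at 10 pairs would have about 80% at rho = 0.8 and 89% at rho = 1.

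**4. Baseline adjustment.** Take the regression of the within-pair follow-up difference on the within-pair baseline difference, with the intercept as the effect. With the slope treated as known, V = V_post − cov²/V_base, which suggests 80% to 90% power at 10 pairs. The slope has to be estimated, however. That inflates the variance by about 1 + 1/(m − 3), or 14% at m = 10, and costs one degree of freedom. Simulating the regression for PPH near miss (100,000 runs, m − 2 degrees of freedom) gives:

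| rho | 10 pairs | 9 pairs |
|---|---|---|
| 0 | 73% | 67% |
| 0.5 | 76% | 70% |
| 0.8 | about 81% | 74% |
| 1 | about 84% | 79% |

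This is above DiD at every rho tried. It is above the plain paired t test only when rho is well above 0.5.

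**The case against.** The strongest reply is that the conflict is partly one of wording. A paired t test on within-district changes would satisfy the abstract and would also be a cluster-level DiD. That is fair, but the article does not say it, the time series is still a further estimator, and the DiD figures above already assume a paired contrast. Reconciling the text this way would therefore leave the power gap.

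A second reply is that the shortfall depends on conditions the article leaves open, and this stands. Table 1 lists overall near miss among the primary indicators. The Discussion speaks of a two-country trial, and the sentence about separate country results sits in the provider-skills paragraph, so pooling is not excluded. The 3000 deliveries are an entry minimum, although the calculation plans on them. Pairs were also balanced on a baseline near-miss indicator. That indicator is a ratio among women with PPH, not per delivery, so how far it shrinks the DiD penalty is unknown.

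A reader might go further and infer three things that the article does not support:

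- *That the trial is underpowered whatever the analysis.* The paired follow-up comparison has the stated power at 10 pairs.
- *That the analyst is free to choose after seeing results.* Analytical methods says an analytical plan is being prepared for advisory-board review, and that plan is not shown.
- *That a time series must fail because it cannot estimate district slopes.* No slope model is specified.

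DiD is also unbiased under randomisation, so the choice between it and the alternatives is one of precision.

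**Conclusion.** The point holds in a conditional form. The abstract and Analytical methods commit to different main analyses, and the 80% power was computed for the paired follow-up comparison alone.

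For PPH near miss analysed by country, DiD falls short of 80% at every between-period correlation, by 9 to 37 percentage points at 10 pairs. This rests on the plan's rates and k, on k applying within pairs as the formula uses it, on about 2000 baseline deliveries per district, and on matching that does not closely balance the baseline per-delivery rate. It does not carry over to overall near miss once the correlation is a little above 0.5 with 10 pairs, nor to a pooled analysis of 19 pairs once it reaches about 0.3.

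Baseline adjustment should not be presented as free. At 9 or 10 pairs it can cost power relative to the plain paired t test.

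**What to change.** Name one primary analysis that uses the pairs, and make the abstract and Analytical methods agree on it.

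- **Primary.** The choice that matches the stated power is a cluster-level paired t test of the 9-month follow-up rate per delivery, with a t-based confidence interval.
- **Supporting.** Pre-specify the baseline-adjusted matched-pair regression. It could be primary instead if the countries are pooled or a high between-period correlation is expected.
- **Supportive only.** The interrupted time series and DiD.
- **If DiD stays primary.** Restate the power for it, giving the assumed between-period correlation, the baseline size, and whether the countries are pooled.

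The cost is wording, with no new data or clusters. The drawback of the paired t test as primary is that it forgoes the gain from baseline adjustment if the correlation turns out to be high: at 10 pairs, about 84% against 80% at the upper limit.

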## Methods/design

### Study design and methodology

The study uses a cluster-randomised design (the Standard Protocol Items: Recommendations for Interventional Trials (SPIRIT) checklist is provided as Additional file 1). We compare ten districts in Tanzania and nine districts in Uganda where the HMS BAB training is being implemented in all hospitals and selected high case-load referral health centres with ten and nine comparison districts in each country respectively that do not receive this training (Fig. 1). All selected facilities undergo a 6-month baseline assessment of the outcomes after which the training intervention is implemented (Fig. 2). All districts, both intervention and comparison, are monitored for a further 9-month period. After this period the facilities in the comparison districts receive the training intervention.

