## Discussion

The evaluation will estimate the effect of the HMS BAB training on maternal mortality and morbidity (near-miss) in a large two-country trial. The study will provide evidence on whether the training programme leads to improved maternal health outcomes. We will also be able to provide information on ’lessons learned’ in implementing the training including the 8-week in-service practice sessions which at medium scale can be used to guide future policy and investments regarding scale-up of training programmes for maternal health in the respective countries. Looking at the evaluation along the implementation pathway will allow us to propose some explanations in case we unexpectedly see no effect of the intervention.

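### If the main outcome is analysed country by country, as the text indicates, Uganda's 9 pairs give about 74–75% power for PPH near miss, not the planned 80%

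*Protocol article*

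**What the plan says.** The Sample size section uses a matched-cluster formula "to calculate the number of clusters needed in order to obtain a power of 80% in our analysis". For PPH near miss it concludes: "we calculated that the required number of clusters required is equal to 10 per group". For overall near miss it requires 8 per group.

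The clusters available are given under Study design and methodology: "We compare ten districts in Tanzania and nine districts in Uganda", each set against an equal number of comparison districts. That makes 10 pairs in Tanzania and 9 in Uganda. The Randomisation section pairs and allocates districts within each country.

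Three statements bear on how the countries are analysed:

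- Analytical methods: "Results will be presented as effect estimates with 95% confidence intervals and will be done separately for each country".
- Analytical methods, next paragraph: "Comparing outcomes calculated at the cluster level is recommended if the cluster size is limited to 18–20 clusters". The trial has 18 clusters in Uganda and 20 in Tanzania, 38 in all.
- Discussion: the effect will be estimated "in a large two-country trial".

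No 19-pair or country-stratified comparison is described.

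**The concern.** The sample size and the analysis do not fit together on either reading. If each country is analysed alone, the 80% power claimed for PPH near miss does not apply to Uganda, which is one pair short, and Tanzania has no margin. If the countries are pooled, the calculation for 10 per group and the reference to 18–20 clusters describe something other than the analysis to be done.

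The per-country reading also leaves information unused. It produces two tests of the same hypothesis, each with power near or below 80%. Suppose that the 25% reduction is true in both countries and that the two tests are independent. The chance that both are significant is then 0.745 × 0.799 ≈ 60%. The chance that exactly one is significant is 0.745 × 0.201 + 0.255 × 0.799 ≈ 35%. A training that works in both countries would give a split result about one time in three.

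**Working it through.** **Inputs, all from the Sample size section.** The section states "assuming a power of 80% and 5% error", that is z-values of 1.96 and 0.84. It gives p0 = 0.02 ("Considering the prevalence of near-miss haemorrhage equal to 2% in the comparison group"), p1 = 0.015 (a 25% reduction), n = 3000 deliveries per cluster and k = 0.15.

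**Step 1: reproduce the stated requirement.** The formula is c = 2 + (1.96 + 0.84)² × V / (p0 − p1)², with V = p0(1 − p0)/n + p1(1 − p1)/n + k²(p0² + p1²).

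- Sampling part: 0.0196/3000 + 0.014775/3000 = 1.146 × 10⁻⁵
- Between-cluster part: 0.0225 × 0.000625 = 1.406 × 10⁻⁵
- V = 2.552 × 10⁻⁵
- c = 2 + 7.84 × 2.552 × 10⁻⁵ / 2.5 × 10⁻⁵ = 10.003, stated as 10

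For overall near miss (6% against 4.5%) the same formula gives 7.56, stated as 8. Both figures reproduce.

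**Step 2: invert the formula for the pairs available.** Power = Φ( √[(c − 2)(p0 − p1)² / V] − 1.96 ).

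| Pairs | Square-root term | Power, PPH near miss |
|---|---|---|
| 9 (Uganda) | √(7 × 2.5/2.552) = 2.619 | 74.5% |
| 10 (Tanzania) | √(8 × 2.5/2.552) = 2.799 | 79.9% |
| 19 (both) | √(17 × 2.5/2.552) = 4.081 | 98.3% |

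A noncentral t calculation for the paired test gives 73.9% for 9 pairs (8 degrees of freedom). For 19 pairs it gives 98.2% with 17 degrees of freedom, one being spent on the country stratum. Replacing the formula's 2 by 3 or 4 for 19 pairs gives 97.7% or 96.9%.

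**Step 3: overall near miss.** At k = 0.15, 9 pairs give 88.1% and 19 pairs 99.8%. Uganda is not short for this indicator.

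**Step 4: sensitivity for PPH near miss.** The values of k and n below other than 0.15 and 3000 are assumptions; they are not in the article.

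| Varied input | 9 pairs | 10 pairs | 19 pairs |
|---|---|---|---|
| k = 0.20 | 59% | 65% | 93% |
| k = 0.25 | 46% | 51% | 83% |
| k = 0.30 | 36% | 41% | 71% |
| n = 2000 | 66% | 72% | 96% |
| n = 4000 | 79% | 84% | 99% |

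**The case against.** **Where the sentence stands.** The sentence on separate results comes directly after the multilevel models for provider skills. The main-analysis paragraph before it names no country split. A reader might infer that the article expressly orders a per-country primary test, or rules out pooling. It does neither. The per-country reading is still well supported: the next sentence concerns the primary outcomes, 18–20 is the cluster count of a single country, randomisation is separate, and a requirement of 10 per group matches one country and not 19 pairs.

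**The analysis plan.** The article mentions a separate analytical plan, which may settle how the countries are combined. For that reason the lack of a rule for discordant countries is not charged here as an omission. The mismatch between the stated requirement and Uganda's 9 pairs lies in the article itself.

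**Separate analysis is defensible.** Randomisation is by country, the calendars lie about a year apart, and the mix of facilities differs. This argues for keeping country estimates, not for leaving 19 pairs without a joint comparison.

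**The shortfall is small and could vanish.** It is one pair, about 5 points, and for one of the listed primary indicators. The 3000 deliveries are a minimum in the inclusion criterion, and matching may lower the variation that matters. With about 4,200 deliveries per cluster, 9 pairs reach 80%; with k = 0.13 they reach 80.5%. Both values are assumptions, and the inputs could equally err the other way, as the sensitivity table shows.

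**Two further inferences fail.** A reader might think that only a k above 0.15 endangers the target. In fact Uganda is below it at k = 0.15 and Tanzania sits on it. A reader might also think that the data are already in hand. The article has Tanzania's endline in progress and Uganda's not yet started.

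**Conclusion.** The point holds as a conditional one. If the main outcome is analysed per country, which the article indicates without expressly saying so, Uganda's power for PPH near miss is about 74–75% and not 80%, on the article's own inputs. Tanzania is at 79.9%. Uganda's 9 pairs are enough for overall near miss.

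The loss of about 5 points in Uganda is the smaller part. The larger part is that 19 pairs would give about 98%, provided that k = 0.15 and the 25% reduction hold in both countries. If k were 0.25, pooling would still give about 83%, against 46% for Uganda alone.

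The documents do not support the conclusion that the trial as a whole is underpowered, or that any estimate would be biased. The weight is moderate: this should be corrected, but it does not undermine the trial.

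**What to change.** 1. In Analytical methods, name one primary comparison for PPH near miss: a matched-pair analysis over all 19 pairs, stratified by country. Pairs are formed within country, so this respects the randomisation.
2. Report country-specific estimates and a country-by-treatment interaction as secondary. The interaction should be read as descriptive. With equal variance per pair, the between-country difference has variance proportional to 1/9 + 1/10 = 0.211, against 1/19 = 0.053 for the pooled effect, so its standard error is about twice as large.
3. In Sample size, state the power for PPH near miss at k = 0.15 as about 74–75% for Uganda alone, 79.9% for Tanzania alone and about 98% pooled. Add a range for k, labelled as assumed (for example 93% pooled at k = 0.20 and 83% at k = 0.25).
4. Say which analyses the sentence on separate country results covers.

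The cost is wording and restated figures. No clusters or data are needed beyond what the trial collects anyway. Uganda's endline had not begun when the article was written, so the choice could be fixed before the full results existed. The small downside is that the pooled estimate averages over two countries whose effects may differ, which is why the country estimates stay in the report.
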